## 2.6 Supplementary Figure S6: Significant Microbiota Features between Baseline and Study End

[figure not shown]

Paired group comparison of relative abundance (a) and prevalence (p) of bacterial taxa between baseline and end of study, including data from either study arm or both study arms. Negative effect sizes (blue) indicate features that a higher at study end compared to baseline while positive effect sizes (red) are lower at study end compared to

baseline. Effect sizes are the bias-corrected coefficients from the linear models, except for alpha diversity metrics which were not subjected to compositional bias correction.

## 2.7 *Supplementary Figure S7: Intra-twin pair Bray-Curtis dissimilarity between visits*

[figure not shown]

Intra-twin pair Bray-Curtis dissimilarity between visits (top left), visits by zygosity (top right), visits – monozygotic (bottom left), visits – dizygotic (bottom right)

## 2.8 Supplementary Figure S8: Microbiota features significantly correlated with physical ability

Correlation to CST

[figure not shown]

Partial Pearson correlations between physical ability (chair rise time) and microbiota feature abundance (a; blue dots) and prevalence (p; orange dots) adjusted for study arm allocation and twin pair. Correlation coefficients are calculated after bias-correction for taxonomical features (species, genus, family, order) while gut metabolic

modules (GMM), gut brain modules (GBM), and alpha diversity (AlphaDiv) coefficients have not been subjected to bias correction. CST: chair stand time (aka chair rise time).

## 2.9 *Supplementary Figure S9: Changes in Microbiota features significantly correlated with change in physical and cognition*

[figure not shown]

Partial Pearson correlations between the change in physical ability (chair rise time, CST; left) and cognition factor score (F, right) and microbiota feature abundance (blue dots) at study end adjusted for relative abundance at baseline, study arm, and twin pair. Change in chair rise time and cognition factor score were calculated as observations at study end minus observations at baseline. Correlation coefficients for taxa are calculated after bias-correction. AlphaDiv: alpha diversity.

## 2.10 Supplementary Figure S10: Microbiota features significantly correlated with cognition

[figure not shown]

Partial Pearson correlations between cognitive ability (cognition factor score, F) and microbiota feature abundance (a; blue dots) and prevalence (p; orange dots) adjusted for study arm allocation and twin pair. Correlation coefficients are calculated after bias-correction.

### 3 Supplementary Tables

#### 3.1 Supplementary Table S1: Demographic characteristics of those who declined or were ineligible to take part, versus those who took part.

|                  |                    | Declined/Ineligible                | Study Participant | p-value |
|------------------|--------------------|------------------------------------|-------------------|---------|
|                  |                    | N=525                              | N=72              |         |
|                  |                    | Declined n=326
Ineligible n=199 |                   |         |
| Age (years)      |                    | 75 (5)                             | 73 (5)            | 0.006*  |
| Sex              | Female             | 479 (91%)                          | 56 (78%)          | <0.001* |
|                  | Male               | 46 (9%)                            | 16 (22%)          |         |
| Zygosity         | Monozygotic        | 299 (57%)                          | 44 (61%)          | 0.50    |
|                  | Dizygotic          | 226 (43%)                          | 28 (39%)          |         |
| Smoking Status   | Never Smoked       | 299 (57%)                          | 38 (53%)          | 0.48    |
|                  | Ex-Smoker          | 206 (40%)                          | 30 (42%)          |         |
|                  | Current Smoker     | 16 (3%)                            | 4 (6%)            |         |
| Household Income | Declined to Answer | 108 (23%)                          | 13 (18%)          | 0.24    |
|                  | Low Income         | 200 (43%)                          | 30 (42%)          |         |
|                  | Middle Income      | 102 (22%)                          | 23 (32%)          |         |
|                  | High Income        | 56 (12%)                           | 6 (8%)            |         |
| Education Level  | Low                | 239 (48%)                          | 33 (46%)          | 0.95    |
|                  | Middle             | 169 (34%)                          | 25 (35%)          |         |
|                  | High               | 92 (18%)                           | 14 (19%)          |         |
| Weight (kg)      |                    | 71.9 (14.0)                        | 73.8 (15.7)       | 0.31    |
| Height (m)       |                    | 1.6 (0.1)                          | 1.6 (0.1)         | 0.64    |
| Body Mass Index  |                    | 27.2 (5.1)                         | 28.0 (5.1)        | 0.22    |
| Frailty Index    |                    | 0.3 (0.1)                          | 0.2 (0.1)         | 0.71    |

P values are group comparisons between each study arm performed using a two-sided paired t-test. Data for those who declined or were ineligible is the most recent available data in the longitudinal TwinsUK cohort. The difference between the two groups in terms of sex was adjusted for age, and likewise the difference between the two groups in terms of age was adjusted for sex, to assess whether one of these variables was driving all the variation between the two groups. However, a significant difference was retained in both cases. \* Denotes significance.

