## 10 Study design & Flowchart

### 10.1 Study Design

The proposed study will provide a simple but robust intervention study using protein supplementation and prebiotic food supplementation to improve our understanding of the mechanisms linking nutrition to health outcomes that are mediated by the gut microbiome.

The study will be a randomised, placebo controlled, double blinded, intervention study in which participants will be grouped into two different arms. Randomisation will control for equal distribution of key characteristics that may confound between group comparisons and will be assessed by analysis of pre-existing baseline data. Participants will be randomised as twin pairs, with one twin from the pair in the prebiotic food supplement arm and one twin from the pair in the placebo arm. Twin pairs are matched for age and often for sex, early environment, baseline genetic sequence, socioeconomic status etc., proving a strong model for detecting changes that are truly significant.

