***e. Planned tables and figures***

**i. Table 2: Planned tables and figures**

| Table/Figure | Title                                                     |
|---------------------|------------------------------------------------------------------|
| Figure 1            | Participant Flow Diagram (see 4.3)                               |
| Table 1             | Comparison of participants to those who declined/were ineligible |
| Table 2             | Baseline Characteristics, by study arm (see 4.2.1)               |
| Table 3             | Group wide comparisons between baseline and study end point      |
| Table 4             | Dietary Intakes at baseline and study end                        |
| Table 5             | Cognition Factor Analysis                                        |
| Table 6             | Adverse events, dropouts, compliance                             |
| Table 7             | Linear Mixed models for primary and secondary outcomes           |
| Table 8             | Sensitivity Analyses                                             |
| Table 9             | Subgroup Analyses                                                |
| Table 10            | Validation Analyses                                              |

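### Supplementary Table S1 names a test that cannot apply to its groups, and its p-values treat 72 co-twins as independent people, which overstates the evidence for the age difference

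*Combined protocol and SAP*

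**What the plan says.** The SAP's list of planned tables (section 7, Table 2) includes one titled "Comparison of participants to those who declined/were ineligible" but names no test for it. Supplementary Table S1 is that table. It sets 525 non-participants ("Declined n=326 Ineligible n=199") against 72 participants and stars two rows: age, 75 (5) v 73 (5) years, p = 0.006; and sex, 91% v 78% female, p < 0.001.

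The footnote states that "P values are group comparisons between each study arm performed using a two-sided paired t-test". It adds that the sex difference was adjusted for age and the age difference for sex, and concludes: "However, a significant difference was retained in both cases". It mentions no twin-pair term.

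Elsewhere the documents are clear about the pairing. Protocol section 10.1 says that "Twin pairs are matched for age and often for sex", and both protocol and SAP place one twin of each pair in each arm. For the primary outcome, the SAP (section 7, Primary Outcome) uses the twin-pair identifier, fid, as a random effect because the data are clustered.

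**The concern.** There are two faults, and the first needs no arithmetic. A paired t-test between study arms cannot produce this table: the columns are not arms, they hold different numbers of different people, and five of the rows are categorical. As printed, a reader cannot tell how any p-value was obtained.

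The second is independence. Co-twins have the same zygosity by definition and, for practical purposes, the same age. On those rows the participant column carries 36 independent values, not 72. A test that counts individuals uses a standard error that is too small and rejects a true null too often.

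At stake is the description of who took part. The table supports the statement that participants differ from non-participants in both age and sex, each after adjustment for the other.

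**Working it through.** **Inputs.** Table S1 gives the group sizes (525 and 72), the category counts, the age summaries and the printed p-values. The 72 are 36 complete pairs (36 per arm, one co-twin in each; 44 monozygotic = 22 pairs, 28 dizygotic = 14 pairs). The SAP's threshold is 0.05, and the footnote's test is two-sided. The documents do not say how many of the 525 are in pairs, so the share f is run from 0 to 1. The within-pair correlation ρ is taken as 1 for age and zygosity, with lower values shown for partly shared traits.

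**Step 1: reproduce the printed p-values.** Pearson chi-square without continuity correction, every person independent:

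| Row | Counts, non-participants v participants | Recomputed p | Printed p |
|---|---|---|---|
| Sex | 479/46 v 56/16 | 0.0004 | <0.001 |
| Zygosity | 299/226 v 44/28 | 0.503 | 0.50 |
| Smoking | 299/206/16 v 38/30/4 | 0.480 | 0.48 |
| Income | 108/200/102/56 v 13/30/23/6 | 0.241 | 0.24 |
| Education | 239/169/92 v 33/25/14 | 0.949 | 0.95 |

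All five match. For the two-by-two zygosity row, the continuity-corrected test gives 0.588 and Fisher's exact test 0.528, so neither was used. Independent t-tests on the rounded summaries give 0.21 for BMI (printed 0.22) and 0.29 for weight (printed 0.31).

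**Step 2: the age row.** The rounded figures give p = 0.0015 under independence. A printed 0.006 (z = 2.748) at SD 5 corresponds to a difference of 2.748 × 5 × √(1/525 + 1/72) = 2.748 × 0.628 = 1.73 years. Supplementary Table S3 puts the participants' mean age at (22 × 74.7 + 50 × 72.4)/72 = 73.1, so the non-participant mean would be about 74.8, which prints as 75. With pairs respected, the same p needs 1.73 × 1.37 to 1.73 × 1.41, about 2.4 years. That puts the mean at about 75.5, the edge of what prints as 75. At SD 4.5, the low end of rounding, it needs only 2.1 to 2.2 years, which fits. The age row alone therefore does not settle which test was used. Independence is inferred mainly from the other rows.

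**Step 3: variance ratio with pairing.**

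r = [(1 + fρ)/525 + (1 + ρ)/72] / [1/525 + 1/72]

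At ρ = 1:
- f = 0: (0.00190 + 0.02778)/0.01579 = 1.88, so standard errors are too small by √1.88 = 1.37.
- f = 1: r = 2.00, a factor of √2 = 1.41.

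**Step 4: true type I error at nominal 5%**, 2[1 − Φ(1.96/√r)], as f runs from 0 to 1:
- ρ = 1: 15.3% to 16.6%. A simulation of 40,000 runs with identical values within pairs gave 15.1% and 16.7%.
- ρ = 0.5: 10.2% to 11.0%.
- ρ = 0.3: 8.1% to 8.6%.

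**Step 5: rescaled p-values**, f from 0 to 1:
- Age, ρ = 1: z = 2.748/√1.88 to 2.748/√2, giving p = 0.045 to 0.052.
- Sex, chi-square 12.33: divided by 1.88 to 2.00, p = 0.010 to 0.013 if co-twins were always the same sex. At ρ = 0.5 (r = 1.44 to 1.50), p = 0.003 to 0.004.
- Zygosity, chi-square 0.448: divided by 1.88 to 2.00, p = 0.63 to 0.64.

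**Step 6: when does age cross 0.05?** It needs r = (2.748/1.96)² = 1.966. Since r = 1.879 + 0.121f, this means f ≈ 0.71. Rounding of the printed 0.006 matters as well: 0.0055 to 0.0065 gives 0.043 to 0.047 at f = 0 and 0.0496 to 0.054 at f = 1.

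**The case against.** The strongest reply is that no conclusion demonstrably changes. Sex stays significant in every scenario and zygosity was never significant. Age moves to the threshold but crosses it only if more than about 71% of the 525 are in complete pairs, a figure the documents do not give. The table is also descriptive, its test is not specified in the SAP, and the SAP does model the pairing for the primary outcome. All of this stands, and it limits the importance of the point. It does not rescue the footnote or make the printed standard errors right.

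Four stronger readings are tempting and should be resisted.
- A reader might infer that the age difference itself is exaggerated. Ignoring clustering leaves the estimate unbiased; only its precision is misstated.
- A reader might apply the 15 to 17% error rate to the whole table. It holds for fully shared traits only, and the protocol says pairs are often, not always, of the same sex.
- A reader might conclude that age loses its star. The range straddles 0.05, and the age test is inferred rather than stated.
- A reader might conclude that the sentence on retained significance is false. The adjusted estimates are not printed and could not be recomputed; only unadjusted values were rescaled.

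**Conclusion.** Wrong as written, but minor. The footnote names groups and a test that do not fit the table. The categorical p-values are independent-person tests, and the age p-value very likely is too, on data in which the participants are 36 pairs. The evidence for an age difference is overstated: p is about 0.045 to 0.052 rather than 0.006, which is borderline. The evidence for a sex difference weakens to at most about 0.013 and remains significant.

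These figures assume a within-pair correlation of 1 for age and zygosity, an unknown share of pairs among the 525 (both extremes shown), and, for age, that the printed value came from an independent-person test. Nothing here bears on the primary outcome, the sample size or the randomised comparison.

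**What to change.** - Recompute every row of Supplementary Table S1, and the age-adjusted sex and sex-adjusted age models, with standard errors clustered on family ID (fid), for example by cluster-robust regression or GEE.
- State how many of the 525 non-participants are in complete pairs.
- Correct the footnote to name the groups compared (participants v those who declined or were ineligible) and the tests used for continuous and categorical rows.
- Restate the sentence on retained significance from the recomputed adjusted models, giving the estimates with confidence intervals.

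The cost is one re-run on data already held. P-values will be larger for traits that co-twins share, and the age result may or may not keep its star.

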### ***3.2 Supplementary Table S2: Details of adverse events experienced by participants in the PROMOTe trial.***

| No. | Adverse Event                          | Arm | Related to Study? |
|------------|-----------------------------------------------|------------|--------------------------|
| 1          | Bloated, loss of appetite, waist feels bigger | 2          | probably                 |
| 2          | Bloating                                      | 1          | probably                 |
| 3          | Bloating                                      | 1          | probably                 |
| 4          | Flatulence*                                   | 1          | probably                 |
| 5          | Wind                                          | 1          | probably                 |
| 6          | Constipation                                  | 1          | possibly                 |
| 7          | Diverticulitis                                | 1          | possibly                 |
| 8          | Cramps in legs                                | 1          | remote                   |
| 9          | Headaches                                     | 2          | remote                   |
| 10         | Hair loss*                                    | 1          | remote                   |
| 11         | Nose bleeds                                   | 1          | remote                   |

\*Experienced by same participant. Arm 1 = prebiotic. Arm 2 = placebo.

### 3.3 Supplementary Table S3: Cognition Missingness

|                             |                       | Missing
CANTAB at
baseline | Not
Missing
CANTAB at
baseline | p-
value | Missing
CANTAB at
study end | Not
missing
CANTAB at
study end | p-
value |
|-----------------------------|-----------------------|----------------------------------|-----------------------------------------|-------------|-----------------------------------|------------------------------------------|-------------|
|                             |                       | N=22                             | N=50                                    |             | N=46                              | N=26                                     |             |
| Age                         | Years                 | 74.7 (5.0)                       | 72.4 (4.6)                              | 0.060       | 73.7 (5.2)                        | 72.1 (4.0)                               | 0.180       |
| Sex                         | Female                | 20 (90.9%)                       | 36 (72.0%)                              | 0.075       | 37 (80.4%)                        | 19 (73.1%)                               | 0.470       |
|                             | Male                  | 2 (9.1%)                         | 14 (28.0%)                              |             | 9 (19.6%)                         | 7 (26.9%)                                |             |
| Zygoty                      | Monozygotic           | 11 (50.0%)                       | 33 (66.0%)                              | 0.200       | 28 (60.9%)                        | 16 (61.5%)                               | 0.960       |
|                             | Dizygotic             | 11 (50.0%)                       | 17 (34.0%)                              |             | 18 (39.1%)                        | 10 (38.5%)                               |             |
| Smoking Status              | Never Smoked          | 11 (50.0%)                       | 27 (54.0%)                              | 0.900       | 26 (56.5%)                        | 12 (46.2%)                               | 0.230       |
|                             | Ex-Smoker             | 10 (45.5%)                       | 20 (40.0%)                              |             | 19 (41.3%)                        | 11 (42.3%)                               |             |
|                             | Current Smoker        | 1 (4.5%)                         | 3 (6.0%)                                |             | 1 (2.2%)                          | 3 (11.5%)                                |             |
| Household Income            | Declined to
Answer | 3 (13.6%)                        | 10 (20.0%)                              | 0.920       | 11 (23.9%)                        | 2 (7.7%)                                 | 0.170       |
|                             | Low Income            | 10 (45.5%)                       | 20 (40.0%)                              |             | 18 (39.1%)                        | 12 (46.2%)                               |             |
|                             | Middle Income         | 7 (31.8%)                        | 16 (32.0%)                              |             | 12 (26.1%)                        | 11 (42.3%)                               |             |
|                             | High Income           | 2 (9.1%)                         | 4 (8.0%)                                |             | 5 (10.9%)                         | 1 (3.8%)                                 |             |
| Education Level             | Low                   | 14 (63.6%)                       | 19 (38.0%)                              | 0.110       | 22 (47.8%)                        | 11 (42.3%)                               | 0.570       |
|                             | Middle                | 6 (27.3%)                        | 19 (38.0%)                              |             | 14 (30.4%)                        | 11 (42.3%)                               |             |
|                             | High                  | 2 (9.1%)                         | 12 (24.0%)                              |             | 10 (21.7%)                        | 4 (15.4%)                                |             |
| Alcohol Intake              | Never Drink           | 4 (18.2%)                        | 16 (32.0%)                              | 0.370       | 11 (23.9%)                        | 9 (34.6%)                                | 0.420       |
|                             | Less than
weekly   | 7 (31.8%)                        | 10 (20.0%)                              |             | 10 (21.7%)                        | 7 (26.9%)                                |             |
|                             | At least weekly       | 11 (50.0%)                       | 24 (48.0%)                              |             | 25 (54.3%)                        | 10 (38.5%)                               |             |
| Body Mass Index             | kg/m      | 27.3 (5.5)                       | 28.3 (5.0)                              | 0.420       | 27.7 (5.4)                        | 28.6 (4.6)                               | 0.480       |
| Baseline Protein
Intake  | g/d                   | 58.9 (15.5)                      | 61.5 (13.9)                             | 0.500       | 58.9 (16.2)                       | 63.8 (9.9)                               | 0.170       |
| Baseline
Protein/Weight  | g/kg/d                | 0.9 (0.3)                        | 0.8 (0.2)                               | 0.620       | 0.8 (0.2)                         | 0.9 (0.2)                                | 0.300       |
| Baseline Energy
Intake   | Kcals/d               | 1539.5
(288.7)                | 1582.7
(439.1)                       | 0.670       | 1550.7
(405.8)                 | 1602.8
(388.4)                        | 0.600       |
| Frailty Index               |                       | 0.3 (0.2)                        | 0.2 (0.1)                               | 0.210       | 0.2 (0.1)                         | 0.2 (0.1)                                | 0.980       |
| Baseline Gait speed         | m/sec                 | 1.2 (0.3)                        | 1.1 (0.4)                               | 0.380       | 1.1 (0.4)                         | 1.1 (0.3)                                | 0.430       |
| Baseline Chair Rise
Time | sec                   | 10.7 (4.4)                       | 10.6 (2.8)                              | 0.930       | 10.9 (3.5)                        | 10.0 (2.9)                               | 0.270       |

|                        |               |               |               |       |               |               |       |
|------------------------|---------------|---------------|---------------|-------|---------------|---------------|-------|
| Baseline Grip Strength | kg            | 24.0 (10.3)   | 26.9 (9.4)    | 0.250 | 26.5 (10.4)   | 25.0 (8.5)    | 0.520 |
| Baseline Balance Score |               | 4.0 (0.2)     | 4.0 (0.1)     | 0.550 | 4.0 (0.1)     | 4.0 (0.2)     | 0.680 |
| Baseline SPPB Score    |               | 10.9 (1.8)    | 11.0 (1.3)    | 0.640 | 10.9 (1.6)    | 11.2 (1.3)    | 0.380 |
| Baseline IPAQ          | MET mins/week | 730.6 (756.9) | 650.2 (610.8) | 0.630 | 674.2 (645.4) | 675.9 (683.2) | 0.990 |
| Baseline IPAQ Score    | 1             | 21 (95.5%)    | 48 (96.0%)    | 0.920 | 45 (98%)      | 24 (92%)      | 0.260 |
|                        | 2             | 1 (4.5%)      | 2 (4.0%)      |       | 1 (2%)        | 2 (8%)        |       |
| Baseline SNAQ Score    |               | 14.8 (2.3)    | 15.4 (1.9)    | 0.250 | 15.2 (2.1)    | 15.3 (1.9)    | 0.870 |
| Healthy Eating Index   |               | 60.8 (8.0)    | 59.1 (11.5)   | 0.550 | 61.4 (10.3)   | 56.9 (11.0)   | 0.099 |

CANTAB: Cambridge Neuropsychological Test Automated Battery. SPPB: Short Physical Performance Battery. IPAQ: International Physical Activity Questionnaire. MET: metabolic equivalent of task (One MET is the energy you expend at rest). SNAQ: Simplified Nutritional Assessment Questionnaire. P values are within group comparisons of the total population between baseline and end of intervention performed using a two-sided paired t-test for continuous data and Pearson's chi squared test for categorical data. Analyses were not adjusted for multiple testing.

